### Study design and setting

2.1

This pragmatic, single-arm, multi-site prospective trial employs an implementation-effective hybrid design (Type 2) prioritizing both clinical outcomes and implementation factors (14). The single-arm design was selected over randomized controlled trial designs based on the presence of: (1) extensive existing evidence for RAT equivalent efficacy in comparison with usual care; (2) ethical considerations about withholding potentially beneficial intervention with a randomized control design employing a control group; (3) practical challenges of standardizing rehabilitation treatment control conditions across sites; and (4) the pressing need to evaluate the feasibility, QOL and cost-effectiveness of delivering home-RAT rather than efficacy under ideal or standardised or highly supervised home-training conditions.

The study is conducted across three major public healthcare institutions in Singapore:Tan Tock Seng Hospital (TTSH), National Healthcare Group Health (NHG health): Lead site with Singapore’s first and largest rehabilitation medicine department with extensive rehabilitation technology clinical practice and research experience.Singapore General Hospital (SGH), Singapore Health Services (Singhealth): Nation’s largest hospital with integrated acute-subacute-outpatient rehabilitation servicesNational University Hospital (NUH), National University Health System (NUHS): Academic medical center with Integrated academic health system with strong translational research infrastructure

Each site serves demographically and clinically distinct populations. TTSH predominantly manages older adults with higher neurological complexity through its specialized rehabilitation centre, SGH serves a broad acute-to-chronic case mix through its integrated rehabilitation pathway, and NUH draws from its academic health system catchment with a higher proportion of younger stroke survivors and research-naïve participants. These sites employ different care models, enhancing generalizability while testing implementation robustness across contexts.

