### Statistical analysis plan

2.7

The primary analysis evaluates non-inferiority of the observed utilization rate against a 70% historical benchmark derived from clinic-based RAT programs, with a pre-specified non-inferiority margin of 5%. Non-inferiority is demonstrated if the lower bound of the one-sided 95% confidence interval for the observed utilization rate exceeds 65%. This analysis follows intention-to-treat principles, including all enrolled participants regardless of completion status; participants who withdraw are assigned zero utilization for remaining sessions.

For secondary clinical outcomes (FMA-UE, ARAT, grip strength, EQ-5D-5L, SIS-16, PROMIS-10), linear mixed-effects models are employed with fixed effects for time (categorical: baseline, Week 6, Week 8, Week 12, Week 24), site, and baseline severity (FMA-UE score), and a random intercept for participant to account for within-subject correlation across repeated measures. An unstructured covariance matrix is specified, with model fit compared against compound symmetry using the Akaike Information Criterion. The assumption of normally distributed residuals will be assessed using Q-Q plots and the Shapiro–Wilk test; non-normal outcomes will be analysed using generalized linear mixed models with appropriate link functions. Multiple comparisons across secondary outcomes are controlled using the Benjamini-Hochberg False Discovery Rate procedure at q = 0.05.

Exploratory subgroup analyses examine treatment effect heterogeneity by stroke chronicity (<6 months vs. ≥6 months), baseline severity (FMA-UE < 30 vs. ≥30), age (<65 vs. ≥65 years), and cognitive status (MoCA 21–25 vs. >25) using interaction terms in the mixed models. These are hypothesis-generating and interpreted cautiously given the sample size.

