The economic evaluation calculates incremental cost-effectiveness ratios (ICERs) comparing total costs of the TRUST intervention against usual care (historical cost data), with effectiveness expressed as quality-adjusted life years (QALYs) derived from EQ-5D-5L utility scores. A 12-month Markov model with three health states (independent, dependent, deceased) is constructed, with transition probabilities informed by observed clinical trajectories and published literature. Costs and QALYs are discounted at 3% per annum. Uncertainty is characterised through probabilistic sensitivity analysis using 10,000 Monte Carlo simulations with parameters drawn from appropriate distributions (gamma for costs, beta for utilities, log-normal for relative effects), presented as cost-effectiveness acceptability curves against Singapore-specific willingness-to-pay thresholds. Missing data are handled using multiple imputation by chained equations under the missing-at-random assumption, with sensitivity analyses under missing-not-at-random scenarios.

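### Usual care is tied to a data source for costs only, and single-arm change is labelled treatment effect, so recovery over time risks being read as benefit

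*Protocol article*

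**What the plan says.** All references are to the protocol article.

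- **Design (2.1).** "This pragmatic, single-arm, multi-site prospective trial employs an implementation-effective hybrid design (Type 2) prioritizing both clinical outcomes and implementation factors". One reason given for having no control group is "extensive existing evidence for RAT equivalent efficacy in comparison with usual care".
- **Economic evaluation (2.7).** ICERs are to be calculated "comparing total costs of the TRUST intervention against usual care (historical cost data), with effectiveness expressed as quality-adjusted life years (QALYs", the QALYs being "derived from EQ-5D-5L utility scores". The structure of the decision model is then stated: "A 12-month Markov model with three health states (independent, dependent, deceased) is constructed". Its inputs are covered by one phrase, "with transition probabilities informed by observed clinical trajectories and published literature". The distributions for the probabilistic sensitivity analysis are "gamma for costs, beta for utilities, log-normal for relative effects".
- **Clinical outcomes (2.7).** The mixed models contain time, site and baseline FMA-UE as fixed effects and a random participant intercept. There is no treatment term, as there can be none with one arm.
- **Subgroups (2.7).** "Exploratory subgroup analyses examine treatment effect heterogeneity by stroke chronicity (<6 months vs. ≥6 months", and by severity, age and cognition, through interaction terms. They are called hypothesis-generating, and the reason given for caution is the sample size.
- **Population (Table 1, 1.2).** Entry is open from more than 28 days after stroke with no upper limit. The Introduction says that recovery potential is still high after discharge.
- **Discussion.** The authors accept that one arm limits causal inference and say that historical controls and sensitivity analyses partly make up for it.

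**The concern.** An ICER divides a difference in cost by a difference in QALYs. For usual care the article names where the costs come from, but not where the utilities or the relative effect come from. The trial observes utilities only in treated participants. The most readily available number for the denominator is therefore the change in EQ-5D-5L within the arm, and in a cohort that includes early subacute patients part of that change would have happened anyway.

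The clinical analysis has a related fault that does not depend on any missing input. The subgroup interactions estimate how within-arm change differs between strata, yet they are named as differences in treatment effect. Chronicity is the stratum where this misleads most, because people under 6 months after stroke are expected to improve more with or without a robot.

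Secondary objectives (2), clinical effectiveness, and (3), economic viability, are exposed, and so are the policy conclusions drawn in the Discussion.

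**Working it through.** **1. Is there a plan figure to reproduce?** No. The article states no ICER, incremental QALY, cost difference or usual-care utility. The numbers in steps 3 and 4 are illustrations on assumed inputs.

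**2. What usual-care information does the article fix?**

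| Quantity | Intervention | Usual care |
|---|---|---|
| Cost | collected (2.5.2.4) | historical cost data |
| Utility / QALY | EQ-5D-5L, single arm | no source named |
| Transition probabilities | observed trajectories, literature | literature possible; allocation not stated |
| Relative effect | foreseen in the sensitivity analysis | not estimable from one arm; no source named |
| Historical outcome benchmark | – | 70% utilization only; none for EQ-5D-5L, FMA-UE or ARAT |

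Observed trajectories exist only for treated participants. A relative effect must therefore come from outside the trial or be replaced, openly or not, by within-arm change.

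**3. What if within-arm change is used as the increment?** Let ΔC > 0 be the cost difference, q the QALY gain within the arm relative to a flat baseline utility, and f the share of q that would also occur under usual care.

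- ICER with all change credited = ΔC / q
- ICER with the usual-care share removed = ΔC / [q(1 − f)]
- Ratio of the second to the first = 1/(1 − f), whatever ΔC and q are

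This gives 2 at f = 0.5, 4 at f = 0.75 and 10 at f = 0.9. At f = 1 the ICER is undefined.

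**4. Scale, on assumed utility gains u of 0.05 and 0.10 over the 12-month horizon.**

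- Gain linear to Week 8, then held: q = u × [(8/52)/2 + 44/52] = 0.923u, so 0.0462 and 0.0923 QALY.
- Gain linear to Week 24, then held: q = u × [(24/52)/2 + 28/52] = 0.769u, so 0.038 and 0.077 QALY.
- With an assumed ΔC of 3,000 currency units, u = 0.10 and the Week 8 profile, the ICER is 3,000/0.0923 = 32,500 at f = 0, 65,000 at f = 0.5, 130,000 at f = 0.75 and 325,000 at f = 0.9.
- With u = 0.05 it runs from 65,000 (f = 0) to 650,000 (f = 0.9).

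**5. What does the chronicity interaction estimate?** Write the mean change in stratum s as τ(s) + ν(s). Here τ is the effect of the programme and ν is spontaneous recovery, retest effects and regression to the mean. The interaction is

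[τ(<6 months) − τ(≥6 months)] + [ν(<6 months) − ν(≥6 months)].

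One arm identifies only the sum. If τ is equal in both strata, including zero in both, the interaction equals the difference in ν, which is expected to favour the early stratum. More participants would narrow the confidence interval around this sum but would not remove the second bracket. Caution tied only to sample size therefore misses the main reason for caution.

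**The case against.** **A comparator effect is foreseen.** The evaluation draws on published literature and includes a relative-effect parameter. A reader might infer from the cost-only parenthesis that the ICER has no comparator effect and that recovery will be credited to the robot. The documents do not support that: no rule says usual care is modelled as flat at baseline, and the QALY figures above arise only if it is. This objection stands, and it makes the point one of risk.

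**Input sources and state definitions belong in the full plan.** This also stands. That the article names neither the literature source nor the scale behind the independent and dependent states is no error in itself. What remains is that the article specifies the ratio, the cost-only comparator and the single arm together, and does not exclude the one substitution that would bias the result.

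**Equivalent efficacy does not mean a zero increment here.** A reader might take section 2.1 to imply that true incremental QALYs are near zero. Sections 1.3 and 1.4 describe equivalence at matched dose or duration, and 1.3 allows for an advantage as an adjunct. TRUST adds daily home training, against the sparse post-discharge care described in 1.2. Zero is therefore a reasonable scenario, not the expected value.

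**The ratio's instability is partly handled.** Acceptability curves remain readable when incremental QALYs are small. They still need usual-care QALYs, as net monetary benefit would, so making net benefit the main result is a preference and would not supply the missing input.

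**The causal limit is admitted and the subgroups are exploratory.** Both are true and lower the weight of the point. Neither corrects the label, and the stated caution is about sample size, not the absent control. Resting effectiveness wording on the stratum at 6 months or more would be a trade-off, not a correction: it is still a before-after comparison, and its expected size is not given.

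**Conclusion.** The concern holds in a limited form. The economic plan ties usual care to historical costs only and foresees a relative effect that this trial cannot estimate, so within-arm EQ-5D-5L change, spontaneous recovery included, risks being used as incremental QALYs. If that happened, a positive ICER would be too low by 1/(1 − f). The factor follows from algebra; f, the utility gains and the cost difference are assumptions, and no QALY magnitude can be derived from the article.

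The labelling fault is firmer because it follows from the stated model. Interactions with time in one arm are differences in change. They are not differences in treatment effect, and a larger change under 6 months would not show that the robot works better there.

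The primary utilization analysis is untouched.

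**What to change.** **Economic evaluation (2.7).**

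- State that within-arm change will not serve as the incremental effect.
- Take usual-care utilities and the relative effect from an external source comparable in time since stroke, and vary both in sensitivity analysis.
- Add a scenario with incremental QALY set to 0, reported as a cost comparison. This matches the Discussion's own value case, which is similar clinical results at lower societal cost.

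**Clinical outcomes (2.7).**

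- Replace the treatment-effect label on the interactions with differences in change over time.
- Report change by chronicity stratum.
- State that, without a control, neither the changes nor their differences can be attributed to the intervention, and give this as a reason for caution alongside sample size.

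**Cost.** Revised wording, a sourced set of external inputs and one extra scenario analysis, with no new data collection from participants. The economic and effectiveness claims become more modest.

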### Ethical considerations

2.8

The study received approval from National Healthcare Group Domain Specific Review Board (reference: 2023/00954) with full compliance to Singapore’s Human Biomedical Research Act and ICH-GCP guidelines. Informed consent emphasizes voluntary participation with forms translated into Chinese, Malay, and Tamil, requiring legally authorized representative consent for cognitive impairment (MOCA 21-25) with ongoing assent assessment.

## Discussion

3

This pragmatic trial directly addresses critical barriers that have prevented robot-aided therapy translation despite decades of efficacy evidence. By evaluating home-based delivery using affordable, user-friendly, adaptive technology, we test a fundamentally different implementation model that could democratize access to intensive rehabilitation. The multi-site design across diverse healthcare settings provides natural variation in patient demographics and impairment characteristics, clinical workflows, cost structures and organizational cultures, enhancing confidence that successful results could translate broadly across Singapore’s healthcare system and potentially to similar developed Asian and international contexts. The emphasis on implementation outcomes alongside clinical effectiveness recognizes that pristine efficacy data from controlled trials often fails to predict real-world success, with much evidence-based interventions failing during implementation due to inadequate attention to contextual factors, stakeholder engagement, and sustainability planning.

The combinatory (home-RAT and clinic COT) service delivery model combining home-RAT with scheduled clinic visits and periodic outcome evaluation represents innovation in rehabilitation care architecture. Far from replacing therapists with robots, this approach upskills and repositions clinical rehabilitation professionals as conductors, remotely orchestrating technology-enabled home programs while reserving direct contact for high-value interventions requiring hands-on techniques to translate RAT gains to functional improvements. This could substantially increase therapist’s capacity to serve more patients while maintaining or potentially improving care quality through continuous objective monitoring and data-driven decision making. Furthermore, productivity gains could extrapolate to home situations as only carers were needed to supervise participants if needed during home-RAT.

Comprehensive economic evaluation provides crucial evidence for policy decisions in resource-constrained health systems facing a growing stroke burden. If home-RAT demonstrates comparable clinical effectiveness at lower total societal cost, the value proposition becomes compelling for health system transformation. The inclusion of willingness-to-pay assessment captures patient preferences and perceived value often overlooked in technology adoption decisions but critical for sustainable implementation and appropriate pricing strategies. Success could catalyze multiple policy changes including development of regulatory frameworks for home-based rehabilitation technology, quality standards for remote monitoring and supervision, reimbursement models covering technology-enabled care.

Several limitations warrant consideration when interpreting results. The single-arm design, while pragmatic and ethically justified given existing robust evidence, limits causal inference compared to randomized controlled trials, though comparison with robust historical controls and sensitivity analyses partially address this limitation. The 24-week follow-up may miss important long-term outcomes occurring years after stroke, including durability of gains, and technology abandonment, though cloud performance tracking. Technology requirements including basic internet connectivity and smartphone access may exclude digitally disadvantaged populations, potentially exacerbating health disparities despite efforts to minimize technical barriers through simplified interfaces and comprehensive training. The requirement for stable home environments and available caregivers may exclude vulnerable populations including those living alone or in institutional care, limiting generalizability to those potentially most needing innovative rehabilitation solutions.

This study establishes foundations for multiple future research directions including dose–response optimization studies to individualize therapy parameters, predictive analytics using machine learning to identify optimal patient selection criteria, technology enhancements incorporating artificial intelligence for adaptive difficulty adjustment and automated assessment, and population expansion to other neurological conditions. Implementation science investigations will develop and test strategies for scaling successful models across diverse healthcare contexts, while international collaboration could adapt the approach for low- and middle-income countries where rehabilitation services remain severely limited.

### Risk mitigation measures

3.1

These include progressive home-RAT training protocols with 2-h daily limits, 24/7 research assistant/therapist/technical support with phone advice and replacement devices, multilayered data encryption, and quarterly safety monitoring by an independent committee with remote and phone/messaging advice and replacement pre-specified stopping rules for adverse events >10%, dropout >25%, or technical failures >15%.

## Conclusion

4

The TRUST study represents a much needed and critical investigation at the convergence of rehabilitation science and clinical practice, implementation research, and health system innovation, addressing fundamental questions about the feasibility, acceptability, and cost effectiveness of home-RAT for stroke rehabilitation. By evaluating real-world implementation across diverse clinical settings, this research provides comprehensive evidence needed to inform practice transformation and policy development in an era of demographic transition, technological advancement, and evolving healthcare delivery models. Success would demonstrate that intensive, evidence-based rehabilitation can be delivered effectively in patients’ homes using affordable technology with remote clinical oversight, potentially solving the post-acute rehabilitation gap that compromises recovery for millions of stroke survivors globally.

The study’s comprehensive approach encompassing clinical outcomes, economic evaluation, technology acceptance, and implementation factors provides the multifaceted evidence required for complex health system interventions. Beyond immediate clinical implications, findings will contribute to broader understanding of how healthcare systems can leverage technology to address workforce limitations, demographic pressures, and patient preferences while maintaining or improving care quality and equity. The convergence of portable robotics, telehealth infrastructure, and implementation science creates unprecedented opportunities to transform rehabilitation delivery rehabilitation outcomes: telehealth and positions Singapore as a leader in telerehabilitation robotics.
